**Figure 3 fig3:**
[figure not shown]
Combined c-tDCS and fNIRS recording at T0. **(A)** depicts the location of anode. **(B)** shows the settings for c-tDCS and fNIRS recording.

The fNIRS data will be acquired using the NirSmart system (Danyang Huichuang Medical Equipment Co., Ltd., Jiangsu, China). This system continuously monitored concentration changes of oxygenated hemoglobin (HbO) and deoxygenated hemoglobin (HbR) in the cerebral cortex. The apparatus comprised dual-wavelength near-infrared light sources (730 nm and 850 nm light-emitting diodes, LEDs) and avalanche photodiodes (APDs) as detection elements. A configuration of 12 source optodes and 10 detector optodes generated 24 measurement channels. Source-detector separation averaged 3.0 cm (range: 2.7–3.3 cm) across all channels, with hemodynamic data sampled at 11 Hz (Figure 4). Channel coordinates and corresponding brain region calibrations are detailed in Supplementary Table 1.

**Figure 4 fig4:**
[figure not shown]
Schematic of the custom fNIRS cap design showing 24 channels covering prefrontal and sensorimotor cortices.

This study will focus on hemodynamic monitoring within the prefrontal cortex (PFC) and parietal cortex. The data preprocess includes eliminating irrelevant time intervals and motor artifacts, converting the light intensity to optical density, converting the optical density to blood oxygen concentration. The beta value of each ROI will be calculated by general linear model (GLM) in NirSpark software to reflect the hemodynamic response. The concentration of HbO and HbR is calculate based on the Beer–Lambert law and exported to MATLAB R2018a (MathWorks, USA) for further lateralization analysis.

Lateralization Index = (WA affected - WA unaffected)/(WA affected + WA unaffected).

Among the above formulate, the affected wavelet amplitude (WA) is the average WA value of the cortical regions in the lesional hemisphere, while the unaffected WA is the average WA value of the corresponding cortical regions in the contralesional hemisphere. The value range of the WA side degree is −1 to 1. If it is positive, it indicates that the cortical activity on the lesional side is greater than that on the contralesional side; if it is negative, it indicates that the activity on the contralesional side is greater than that on the lesional side.

#### TMS-MEP data measurement and analysis

The TMS is used to assess excitability of bilateral M1 via MEPs. The hand area of both contralesional and ipsilesional M1 will be stimulated using a figure-of-eight coil (70 mm) connected to magnetic stimulators via a BiStim module (NS1000, Yiruide Group, China). The abductor pollicis brevis (APB) cortical hotspot will be operationally defined as the scalp position eliciting MEPs≥50 μV peak-to-peak amplitude in 5 of 10 consecutive stimuli at minimal stimulator intensity. This site will be marked with a surgical pen and retained for follow-up sessions. Resting motor threshold (RMT) will be determined as the minimum intensity required to evoke MEPs >50 μV in 5/10 trials during complete muscle relaxation for both hemispheres. Subsequently, ten MEPs will be recorded at 120% of the RMT from both the contralesional and ipsilesional M1 while the APB is at rest. The peak-to-peak amplitude (in microvolts) and latency (in milliseconds) of these MEPs will be averaged for analysis. The interhemispheric ratio of MEP amplitude (ipsilesional/contralesional) will be calculated as a measure of interhemispheric balance.

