### Hypotheses

We hypothesize that: (1) Participants receiving active anodal c-tDCS combined with CULR will demonstrate significantly greater improvement in UE motor function compared to those receiving sham c-tDCS with CULR. (2) Active c-tDCS will induce greater normalization of cortical hemodynamics, as measured by fNIRS, characterized by a shift in the laterality index. (3) Active c-tDCS will modulate corticospinal excitability, leading to increased MEP amplitudes from the ipsilesional M1 and a more balanced interhemispheric MEP ratio.

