4. MMSE>21	
5. Moderate to severe upper limb motor impairment, defined as a baseline Fugl-Meyer Assessment for the Upper Extremity (FMA-UE) score between 0 and 40	

Complete assessments will be performed at T0, T1, and T2 for both groups (Figure 2 and Table 2).

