### Statistical analysis

The primary analysis will follow the Intention-to-Treat (ITT) principle, including all randomized participants in the groups to which they were originally assigned. For the primary outcome (FMA-UE), missing data will be handled using multiple imputation. A per-protocol (PP) analysis will also be conducted as a sensitivity analysis. To test the primary hypothesis, a mixed-model Analysis of Variance (ANOVA) with factors for Group (active, sham) and Time (T0, T1, T2) will be used to test for the crucial Group x Time interaction effect.

Descriptive statistics will be employed to characterize participants’ clinical profiles. Between-group comparisons will be performed using chi-square tests for categorical variables and independent samples t-tests for continuous variables. Prior to parametric testing, data normality and variance homogeneity will be assessed using the Kolmogorov–Smirnov test and Levene test in the SPSS. All statistical analyses will be performed using SPSS software (version 20.0; SPSS Inc., Chicago, IL, USA). A *p*-value <0.05 will be considered as statistically significant. In addition to the primary analysis, exploratory subgroup analyses will be conducted based on baseline impairment severity (FMA-UE score: moderate [20–40] vs. severe [0–19]) to investigate potential differential treatment effects.

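### The MEP outcomes have no defined ipsilesional value when no MEP can be evoked, although eligibility reaches FMA-UE 0 and sets no MEP criterion

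*Protocol article*

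**What the plan says.** Table 1 of the protocol article (inclusion criterion 5) sets moderate to severe impairment, "defined as a baseline Fugl-Meyer Assessment for the Upper Extremity (FMA-UE) score between 0 and 40". No criterion in that table concerns MEPs. The Statistical analysis section plans a subgroup with FMA-UE 0 to 19, so severely impaired patients are expected and not merely tolerated.

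The section on TMS-MEP data measurement and analysis sets out a chain of steps:

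- The hotspot is the "scalp position eliciting MEPs≥50 μV peak-to-peak amplitude in 5 of 10 consecutive stimuli at minimal stimulator intensity".
- RMT is the "minimum intensity required to evoke MEPs >50 μV in 5/10 trials during complete muscle relaxation for both hemispheres".
- Then "ten MEPs will be recorded at 120% of the RMT from both the contralesional and ipsilesional M1 while the APB is at rest", and their amplitude and latency are averaged.
- Finally, "The interhemispheric ratio of MEP amplitude (ipsilesional/contralesional) will be calculated as a measure of interhemispheric balance".

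Table 2 lists RMT, amplitude, latency and the ratio as secondary outcomes at T0, T1 and T2. Hypothesis 3 expects active stimulation to change corticospinal excitability, "leading to increased MEP amplitudes from the ipsilesional M1 and a more balanced interhemispheric MEP ratio". The Statistical analysis section states multiple imputation for FMA-UE only. The Randomization and blinding section places allocation after the T0 assessments.

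**The concern.** Each step of the chain presupposes the one before it, and the first presupposes that an MEP can be evoked. The eligibility criteria do not ensure this in the lesioned hemisphere. Where it fails, the article offers no amplitude of 0, no convention at maximum stimulator output and no present/absent endpoint.

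Two things are at stake for hypothesis 3. First, its two named measures, ipsilesional amplitude and the interhemispheric ratio, do not exist for part of the eligible population. Second, a patient who has no MEP at T0 and regains one by T1 shows the hypothesised effect most plainly, yet cannot be counted as a gain. Such a patient has no T0 value and, if included at T1 alone, is likely to add a small amplitude to the average. An absent MEP is also an observed state and not a lost measurement, so imputing a value for it would not be a natural repair.

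**Working it through.** **1. Following the definitions for a patient with no ipsilesional MEP**

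| Step in the TMS section | Requires | Result |
|---|---|---|
| Hotspot | at least 50 μV in 5 of 10 stimuli | no site, and none to retain for follow-up |
| RMT | over 50 μV in 5 of 10 trials | no value |
| Ten MEPs at 120% of RMT | an RMT | cannot be carried out |
| Amplitude, latency | those ten MEPs | no value |
| Ratio | ipsilesional amplitude as numerator | no value |

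The contralesional RMT, amplitude and latency are unaffected.

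**2. A second route to no value.** Delivering 120% of RMT within 100% of stimulator output needs RMT ≤ 100/1.2 = 83.3%. A patient with an MEP but a higher RMT has an RMT, but cannot be given the stimuli from which amplitude and latency are averaged. No rule covers this.

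**3. How many patients.** The article gives no MEP-absent share. I assume 20%, 40% or 60% for illustration. The Sample size section gives 70 participants and 20% attrition; the abstract gives 48.

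- From 70: 70 × 0.8 = 56 completers. With MEPs present in 80%, 60% or 40%: 44.8, 33.6 or 22.4, so about 45, 34 or 22.
- From 48: 48 × 0.8 = 38.4. The same shares leave 30.7, 23.0 or 15.4, so about 31, 23 or 15.

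The article makes no power claim for MEP outcomes, so there is no planned figure to reproduce. Its f = 0.4 comes from upper-extremity recovery, and I do not carry it over.

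**4. What selection on later MEP presence would do.** Assumptions: latent excitability is standard normal at T0; T0–T1 correlation 0.8; true effect of active stimulation at T1 0.5 SD; an MEP is present when excitability exceeds a threshold t set by the share absent at T0.

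For T1 values compared only where an MEP is present at T1, the sham mean is φ(t)/[1 − Φ(t)] and the active mean is 0.5 + φ(t − 0.5)/[1 − Φ(t − 0.5)]. With 40% absent, t = −0.253:

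- Sham: 0.386/0.600 = 0.644.
- Active: 0.5 + 0.300/0.774 = 0.888.
- Difference: 0.888 − 0.644 = 0.24, against a true 0.5.

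Simulation under the same assumptions (2,000,000 draws per row) gives:

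| Absent at T0 | T1 values, MEP present at T1 | Change, MEP present at T0 and T1 | Analysable at both, active / sham | Regained by T1, active / sham |
|---|---|---|---|---|
| 20% | 0.33 | 0.45 | 78% / 73% | 13% / 7% |
| 40% | 0.24 | 0.42 | 57% / 50% | 20% / 10% |
| 60% | 0.18 | 0.38 | 37% / 30% | 23% / 10% |

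Both comparisons understate the true 0.5. The analysable share differs by arm because presence at T1 is itself affected by treatment. The regained MEPs in the last column do not enter the change analysis at all.

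**The case against.** The strongest reply is that the article nowhere says that patients without an MEP are dropped. It is silent on how MEP data are analysed, and missing-data rules for secondary outcomes are commonly left to an analysis plan that is not shown. That stands: a complete-case analysis is a possible consequence of the definitions, not a stated plan. It does not remove the point, because the measurement rule itself is fixed in the article and cannot be carried out for some eligible patients. If presence or absence is not recorded at each visit, a later analysis plan cannot recover it.

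Three stronger readings are tempting, and the documents do not support them.

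- **That randomisation is broken for hypothesis 3.** T0 precedes allocation. An analysis limited to patients with an MEP at T0, with all of them followed through, keeps a randomised comparison and costs power and generalisability. Bias arises only if presence at T1 or T2 decides who is analysed.
- **That a real effect would change sign.** Amplitudes can be chosen to make the measured-only mean move the wrong way. Take 28 patients, 14 with 400 μV throughout and 5 who regain 100 μV. The measured-only mean falls from 400 to (5,600 + 500)/19 = 321 μV, while the all-patient mean with absent scored as 0 rises from 5,600/28 = 200 to 6,100/28 = 218 μV. Those inputs are invented, describe one arm only and allow no gain among the 14. The simulation shows attenuation in every case and no reversal.
- **That the ratio must be replaced.** Once an absent ipsilesional MEP is scored 0 and the contralesional MEP is present, the ratio is 0, which is a defined value. A bounded index is a preference.

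**Conclusion.** The point holds as a defect in the outcome definition. The TMS section fixes a procedure that yields no ipsilesional RMT, amplitude, latency or ratio when no MEP can be evoked. Eligibility does not exclude such patients, and nothing else in the article handles them. Hypothesis 3 is therefore not defined for part of the eligible sample, and a regained MEP cannot register as a gain from T0.

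The size cannot be established from the documents. It depends on the MEP-absent share, which is assumed here at 20% to 60%, and on whether later MEP presence ends up selecting the analysed patients. If it does, the illustration suggests an estimate of 0.18 to 0.45 SD where the truth is 0.5 SD, under the normal model and correlation assumed above. The affected outcomes are secondary and mechanistic; FMA-UE is untouched. The change is worth making before data collection, but the primary conclusion of the trial does not depend on it.

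**What to change.** In the TMS-MEP section:

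1. Record MEP presence or absence for each hemisphere at T0, T1 and T2, tested up to maximum stimulator output.
2. Score an absent MEP as amplitude 0, which gives a ratio of 0 when the contralesional MEP is present. Keep the patient in the amplitude and ratio analyses, using a rank-based or two-part method.
3. Compare MEP presence at T1 between arms, adjusted for presence at T0, so that regained MEPs count.
4. State what is recorded for a patient who has an MEP but whose 120% of RMT exceeds maximum output.
5. Report RMT and latency only descriptively, in patients with a measurable MEP.

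A bounded index, (ipsilesional − contralesional)/(ipsilesional + contralesional), is optional. It has the same form as the fNIRS lateralization index already in the article.

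The cost is a presence/absence item per hemisphere on the case report form, some sentences of protocol text, one added binary endpoint and slightly more analysis work. The drawbacks are a spike at zero in the amplitude data, and that zeros found at maximum output are pooled with amplitudes taken at 120% of RMT. The protocol should acknowledge both.

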#### Interventions

In this study, conventional rehabilitation training is combined either with active tDCS in experimental group or sham tDCS in the control group. The experimental group receive c-tDCS for 10 days, with 20 min per day, while the control group receive pseudo-stimulation of the same duration. The ipsilesional cerebellar hemisphere is stimulated by the anodal tDCS with current intensity of 2 mA. The anode is placed vertically 3 cm lateral to the middle line at the inion level. The ipsilesional cerebellar hemisphere is stimulated by the anodal tDCS with a current intensity of 2 mA. The anode (5 cm×7 cm) is placed vertically 3 cm lateral to the inion. The cathode (5 cm ×7 cm) will be placed over the ipsilateral upper trapezius. In the control group, there is a gradual increase and decrease process of the current at the beginning and end, imitating the scalp discomfort when the current is initiated to ensure the accuracy of the blinding method.

The CULR of the paretic upper extremity includes electrical neuromuscular stimulation, active or passive range of motion training, and muscle strength training. Each CULR session will last for 45 min, delivered by a professional occupational therapist immediately after each tDCS session. The session will be structured as follows: ~15 min of neuromuscular electrical stimulation and passive/active-assisted range of motion exercises for the shoulder, elbow, wrist, and fingers; ~20 min of task-oriented training (e.g., reaching, grasping, manipulating objects of different sizes and weights); and ~10 min of muscle strengthening exercises using resistance bands or light weights. Both groups will receive the same standardized CULR procedure.

## Outcomes

### Primary outcomes

The FMA-UE is a standardized clinical evaluation tool focusing on motor function of the upper extremity (15), comprising 33 assessment items. This scale employs a 3-point scoring criterion (0 = cannot perform; 1 = partially performs; 2 = fully performs), with a total score range of 0–66, where higher scores indicate better motor function (16). Previous studies have demonstrated its excellent validity and reliability (16), establishing it as a robust instrument for assessing post-stroke upper extremity motor impairment. The application of FMA-UE in this study aims to evaluate the clinical efficacy of tDCS targeting the cerebellum in improving upper extremity function after stroke. A change of ≥ 4.25–5.25 points on the FMA-UE will be considered the minimal clinically important difference (MCID) for interpreting the results, based on established values for the stroke population.

### Secondary outcomes

The fNIRS of the cerebral cortex: This study employs a portable 24-channel fNIRS system to noninvasively monitor cortical activity. Key measured parameters include the concentration changes of HbO and HbR. Signal processing involves continuous wavelet transform (CWT) of the HbO to compute WA within the 0.01–0.08 Hz frequency band across cortical regions (17). The inter-hemispheric laterality index (LI) will be then calculated based on WA to evaluate the degree of brain activation transfer from the affected side to the healthy side. WA-derived LI will be calculated based on the HbO concentration pre- and post-intervention by the same computing method.

The TMS-MEP Assessment: TMS is a standardized neurophysiological technique for evaluating the excitability of M1 (18). In this study, RMT is first determined, defined as the minimum stimulation intensity required to elicit MEPs with a peak-to-peak amplitude ≥50 μV in at least five out of ten consecutive trials while the target muscle remains completely relaxed.

Overall, this study employs a multimodal neurophysiological approach combining fNIRS for assessment of cortical hemodynamic responses and TMS-MEP quantitative evaluation of cortical excitability. This integrative methodology provides compelling evidence to elucidate the neuromodulatory mechanisms underlying c-tDCS-induced upper extremity UE motor function changes following stroke (Table 2).

### Data management

Following data management protocols will be strictly adhered to. Firstly, all subject research data will be assigned to unique codes and recorded in case report forms to protect the confidentiality of the participants. Original documents including informed consent forms, medical records, research records, and routine laboratory reports will be archived by the medical institution. These records will be maintained for a minimum of 10 years following study completion, with electronic archiving permitted when security requirements is satisfied. Hospitalization records during the treatment period will be preserved by the research investigator in accordance with standard medical record retention policies. Monitoring of study conduct and data collection will be performed by the committee of the University Clinical Trial Unit on an annual basis. The raw data collected during this research study will be securely stored for a period of up to 5 years after the publication of the main results paper.

### Statistical analysis

The primary analysis will follow the Intention-to-Treat (ITT) principle, including all randomized participants in the groups to which they were originally assigned. For the primary outcome (FMA-UE), missing data will be handled using multiple imputation. A per-protocol (PP) analysis will also be conducted as a sensitivity analysis. To test the primary hypothesis, a mixed-model Analysis of Variance (ANOVA) with factors for Group (active, sham) and Time (T0, T1, T2) will be used to test for the crucial Group x Time interaction effect.

Descriptive statistics will be employed to characterize participants’ clinical profiles. Between-group comparisons will be performed using chi-square tests for categorical variables and independent samples t-tests for continuous variables. Prior to parametric testing, data normality and variance homogeneity will be assessed using the Kolmogorov–Smirnov test and Levene test in the SPSS. All statistical analyses will be performed using SPSS software (version 20.0; SPSS Inc., Chicago, IL, USA). A *p*-value <0.05 will be considered as statistically significant. In addition to the primary analysis, exploratory subgroup analyses will be conducted based on baseline impairment severity (FMA-UE score: moderate [20–40] vs. severe [0–19]) to investigate potential differential treatment effects.

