### Participants

#### Sample size

Based on an F-test (ANOVA) with the following parameters: a conservative effect size [*f* = 0.4, based on a meta-analysis of tDCS studies for post-stroke UE recovery (13)], *α* error probability = 0.05, power (1-*β*) = 0.95, numerator df = 1, number of groups = 2, the total sample size is calculated in G-power. Accounting for an anticipated 20% attrition rate, the final required sample size is 70 participants, with 35 in each of the two groups.

**Experimental group:** Patients who receive active tDCS for 10 consecutive days with 20 min each day.**Control group:** Patients who receive sham tDCS.

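### The sensitivity analysis named for the imputed ITT result is a per-protocol analysis, which does not vary the assumption about unobserved FMA-UE scores

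*Protocol article*

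**What the plan says.** In the protocol article, the Statistical analysis section sets the primary analysis population: "The primary analysis will follow the Intention-to-Treat (ITT) principle, including all randomized participants in the groups to which they were originally assigned". On missing values it continues: "For the primary outcome (FMA-UE), missing data will be handled using multiple imputation". The next sentence gives the check on that analysis: "A per-protocol (PP) analysis will also be conducted as a sensitivity analysis". The primary hypothesis is tested by the Group x Time interaction in a mixed-model ANOVA over T0, T1 and T2.

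The article names no other sensitivity analysis; the analyses by baseline severity are labelled exploratory. It does not define the per-protocol set, the imputation model or the missing-data assumption. The Sample size section inflates the total with the words "Accounting for an anticipated 20% attrition rate", without splitting that rate by arm or visit.

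**The concern.** A sensitivity analysis should keep the question of the primary analysis and vary an assumption that the data cannot settle. Here that assumption concerns the FMA-UE scores nobody will observe. Standard multiple imputation usually takes them as missing at random, so that participants who leave resemble similar participants who stay. The article does not say this; it is the default reading.

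A per-protocol analysis changes the population instead. It removes participants for what happened after randomisation, so the comparison loses the protection of randomisation, and it assigns no alternative values to missing outcomes. If it agrees with the intention-to-treat result, the imputation assumption has still not been tested. If it disagrees, the difference cannot be traced to missing data, because population and question changed as well. At stake is how firmly the trial can state its primary conclusion if attrition comes near the planned rate.

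**Working it through.** No figure in the plan depends on this choice, so there is none to reproduce. The check compares what each analysis varies and then sizes what goes unexamined.

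**Inputs**
- Attrition: 20% overall (Sample size).
- Total randomised: 70, or 35 per group (Sample size), against 48, or 24 per group if split equally (Abstract). That conflict is a separate matter, so both are shown.
- Minimal clinically important difference: 4.25 to 5.25 points (Primary outcomes).
- Planned effect: f = 0.4 (Sample size), which for two equal groups is d = 2 x 0.4 = 0.8.
- Delta, the amount by which true unobserved scores fall below the imputed ones: not in the article, so an assumption.

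**Step 1. How many outcomes are involved.** 0.20 x 70 = 14 participants; 0.20 x 48 = 9.6, about 10.

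**Step 2. What each analysis varies.**
- Primary: all randomised participants, missing scores imputed under one assumption.
- Per-protocol: a subset chosen on post-randomisation events, with no alternative assumption about missing scores.
- Delta-adjusted imputation: all randomised participants, with that assumption varied over a stated range.

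Only the third bears on the imputation.

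**Step 3. Size of a departure at one visit.** With a missing fraction m in an arm, lowering its imputed values by delta lowers the arm mean by m x delta. The active-minus-sham difference therefore falls by

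m(active) x delta(active) − m(sham) x delta(sham).

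- Active arm only, m = 0.20: 0.20 x 4.25 = 0.85 points; 0.20 x 5.25 = 1.05 points.
- Both arms, equal m and equal delta: 0.20 x delta − 0.20 x delta = 0.

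In the first case each shift is 20% of the delta that produced it, by construction. Truncating scores at 0 can only make an arm's shift smaller.

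**Step 4. Could the conclusion turn on it?** As an approximation, take a two-sample comparison at one visit, in SD units, with 20% missing in each arm and the shift in the active arm only. SE = sqrt(2 / (0.8 x n per arm)), and significance is lost when delta exceeds (d − 1.96 x SE) / 0.20.

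- n = 35: SE = sqrt(2/28) = 0.267. For d = 0.8, delta = (0.8 − 0.524)/0.20 = about 1.4 SD. For d = 0.6, delta = (0.6 − 0.524)/0.20 = about 0.38 SD.
- n = 24: SE = sqrt(2/19.2) = 0.323. For d = 0.8, delta = (0.8 − 0.633)/0.20 = about 0.84 SD. For d = 0.6 the result is not significant even with no shift.

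The conclusion could be robust or fragile depending on the observed effect, and a per-protocol result would not show which. These figures do not convert directly into the Group x Time test over three visits.

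**The case against.** The strongest objection is that this is a condensed article. Missing-data sensitivity analyses and the imputation model are commonly left to the statistical analysis plan, which is not shown, so the absence of a delta-adjusted analysis is no error. That stands. The point rests instead on the role the article does assign: directly after naming multiple imputation, it gives the sensitivity label to a per-protocol analysis.

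It can also be said that the article never claims the per-protocol analysis tests the imputation, and that such an analysis has its own use where treatment departs from plan. The Strength and limitations section foresees current being reduced for some participants. That stands too, and is a reason to keep the analysis in a supplementary role.

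Three further limits on the size hold. The 20% is an overall allowance, not a forecast for the active arm or for a visit. The deltas are illustrative. The shift vanishes when missingness and delta are equal in both arms.

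A reader might infer that the per-protocol set consists of completers, so that both analyses must share the same bias. The set is undefined in the article, so this cannot be established.

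**Conclusion.** The point holds in a limited form. The analysis labelled as the sensitivity analysis cannot show whether the imputed intention-to-treat result is robust to missing data, because it changes the population and leaves the assumption about unobserved scores alone. Under the assumptions shown (20% missing in the active arm, a shift in that arm only), the unexamined movement in the mean difference at a visit is 0.85 to 1.05 FMA-UE points for a delta of 4.25 to 5.25. Severity is minor to moderate.

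Two stronger readings are tempting. One is that the trial will have no other check on missing data; the article alone cannot show this. The other is that the primary result is biased or invalid. Nothing in the article supports that: the intention-to-treat analysis with imputation is unaffected, and missing at random is only inferred.

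**What to change.** Keep the per-protocol analysis, describe it as supplementary, and define its set. As the sensitivity analysis, specify a delta-adjusted multiple imputation on all randomised participants:

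- shift the imputed post-baseline FMA-UE values over a range fixed before unblinding;
- truncate to the scale's limits of 0 and 66, since baseline scores may be as low as 0 and unrestricted subtraction could give impossible values;
- apply the shift in the active arm only, and then in both arms;
- re-run the Group x Time test at each delta and report the delta at which the conclusion changes.

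State the assumption behind the primary imputation in the same place. The range of delta is for the trial team to justify. The cost is a little more analysis and reporting on datasets that will already have been imputed; no new patients or data are needed.

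### The primary Group × Time test has 2 degrees of freedom but the power statement has 1, and no single FMA-UE contrast is named as primary

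*Protocol article*

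**What the plan says.** - **Primary test** (Statistical analysis): a mixed-model ANOVA "with factors for Group (active, sham) and Time (T0, T1, T2) will be used to test for the crucial Group x Time interaction effect". This is named as the test of the primary hypothesis. The same section plans an intention-to-treat analysis with multiple imputation for FMA-UE, and says that "data normality and variance homogeneity will be assessed using the Kolmogorov–Smirnov test and Levene test in the SPSS".
- **Sample size** (Sample size): "Based on an F-test (ANOVA) with the following parameters", namely f = 0.4, alpha 0.05, power 0.95 and "numerator df = 1, number of groups = 2". No number of repeated measurements and no within-patient correlation is given. The result is 70 after 20% attrition, 35 per group.
- **Hypothesis 1** (Hypotheses): patients on active stimulation "will demonstrate significantly greater improvement in UE motor function compared to those receiving sham c-tDCS with CULR".
- **Interpretation** (Primary outcomes): a change of 4.25–5.25 FMA-UE points is the MCID.
- **Visits** (Table 2): FMA-UE is listed at T0, T1 and T2, and none is marked as primary.
- **Order of events** (Randomization and blinding): the envelope is opened after the T0 assessment.

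**The concern.** The power calculation and the primary analysis should describe the same test, and here they do not. The 0.95 is quoted for a 1-df comparison of two groups, while the trial will be judged on a 2-df interaction over three visits.

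The interaction is also an omnibus test. It responds to any difference in the shape of the two FMA-UE profiles: benefit at T1 only, benefit at T2 only, or harm. Hypothesis 1 is narrower, since it predicts greater improvement on active. With no primary visit or contrast named, T1 or T2 could be emphasised after the data are seen. Nor is any one difference in points fixed in advance for comparison with the MCID.

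T0 cannot carry a treatment effect because it precedes allocation. Using it as an outcome level rather than a covariate usually gives up some precision.

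**Working it through.** **1. Degrees of freedom.** (groups − 1)(visits − 1) = (2−1)(3−1) = 2 for the planned interaction, against 1 in the sample size section.

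**2. The plan's own figure.** For a two-group F test the noncentrality is λ = f²N, with 1 and N−2 df. With f = 0.4 (d = 2f = 0.8 for two equal groups) and alpha 0.05:

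- Power 0.95 needs N = 84 (λ = 0.16 × 84 = 13.4, power 0.952), or 84/0.8 = 105 after attrition. The stated 70 is not reproduced.
- With 70 × 0.8 = 56 evaluable, power is 0.836. With 70 evaluable it is 0.910.

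Repeated-measures interaction settings do not give 70 either. At f = 0.4 and correlation 0.5 they need 18 patients (three measurements) or 24 (two) before attrition. Settings that do reach 70 are between-group main effects with repeated measurements. Three measurements at correlation 0.5 give 58, and 58 × 1.2 = 69.6. Two measurements at correlation 0.3 give 56, and 56/0.8 = 70. Both are 1-df tests of the group difference averaged over visits, not the interaction. The document does not say that either was used.

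**3. What the 2-df test responds to.** Assume compound symmetry with correlation ρ, which the documents do not give, and n = 28 per arm. Let the group differences in SD units be (0, d₁, d₂) at T0, T1 and T2. Then λ = (n/2) × Σ(dⱼ − mean)² / (1−ρ), with 2 and 108 df. For (0, 0.8, 0.8) the sum of squares is 0.427, so at ρ = 0.7 λ = 14 × 0.427/0.3 = 19.9. The comparator is ANCOVA at T1, with noncentrality d₁/√[2(1−ρ²)/n] and 53 df.

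| Difference at T1 / T2 (SD) | ρ = 0.5: 2-df, ANCOVA | ρ = 0.7: 2-df, ANCOVA | ρ = 0.8: 2-df, ANCOVA |
|---|---|---|---|
| 0.8 / 0.8 | 0.87, 0.92 | 0.98, 0.98 | 0.999, 0.998 |
| 0.8 / 0.4 | 0.76, 0.92 | 0.94, 0.98 | 0.99, 0.998 |
| 0.4 / 0.8 | 0.76, 0.40 | 0.94, 0.54 | 0.99, 0.69 |

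The 2-df power is unchanged from the first row if the differences are −0.8 / −0.8 (active worse) or 0 / 0.8 (T2 only). The p-value alone does not separate these cases.

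**4. Baseline as covariate.** Per patient, in units of SD², a change from T0 has variance 2(1−ρ), and the baseline-adjusted score has variance 1−ρ². The ratio of adjusted to change is (1+ρ)/2: 0.75 at ρ = 0.5, 0.85 at 0.7 and 0.90 at 0.8.

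**5. Size of trial for a 1-df contrast.** ANCOVA at one visit with d = 0.8, two-sided 0.05 and power 0.95 needs 64, 56, 44 or 32 evaluable patients at ρ = 0.5, 0.6, 0.7 or 0.8. After dividing by 0.8 this is 80, 70, 55 or 40. With 56 evaluable, power is 0.92, 0.96, 0.98 or 0.998. The planned 2-df test needs 74, 60, 46 or 32 evaluable if the effect is fully kept at T2, and 100, 80, 60 or 42 if half is kept.

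**The case against.** **Direction and timing can be read afterwards.** Group means and follow-up comparisons after a significant F would show which arm did better and when, and an article may leave these to the analysis plan. That is fair, and it rules out saying that the analysis cannot reveal direction. It does not supply a primary contrast: the protocol names the interaction itself as the decisive test. Two-sided testing is not the fault either, since the proposed contrast is also two-sided.

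**T0 as an outcome level is legitimate.** In a randomised trial it amounts to an unbiased comparison of changes. This stands; the cost is precision only.

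**A reader might infer that type I error is inflated.** Kolmogorov–Smirnov and Levene tests do not examine sphericity, and simulation under assumed covariances (epsilon about 0.60 to 0.76) gives rejection rates of roughly 6% to 7.5% for an uncorrected F. But the protocol does not say that the F will be left uncorrected, and the covariances are assumptions. With a Greenhouse–Geisser correction the simulated rates were 4.9% and 5.2%. The documents do not support a claim of inflation.

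**A reader might infer that the 2-df test is clearly weaker.** At the plan's own d = 0.8, with correlation 0.7 or more and a sustained effect, it is not. If the effect grows from 0.4 SD to 0.8 SD, the T1 contrast is much the weaker of the two (0.54 against 0.94 at correlation 0.7). Power is not the main argument.

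**T1 is a preference.** The documents rank no visit, so T2 or the T1/T2 average would serve equally if fixed in advance.

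**Conclusion.** The point holds on the text alone in two respects. The primary test has 2 df and the power statement has 1, so the quoted 0.95 does not describe the planned analysis. And the omnibus interaction, taken as the primary result, settles neither that active is better nor when, and supplies no single estimate for Hypothesis 1 or the MCID. Both should be corrected before analysis.

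Baseline adjustment is a lesser improvement: the variance is 0.75 to 0.90 of that of a change score for assumed correlations of 0.5 to 0.8. The power figures rest on assumed correlations, compound symmetry and 28 evaluable patients per arm.

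Two neighbouring problems are separate but bear on the restated power: the stated inputs give 84 (105 with attrition) rather than 70, and the abstract gives 48.

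**What to change.** In Statistical analysis, replace the interaction as the primary test with one contrast, for example: *The primary estimate is the active-minus-sham difference in mean FMA-UE at T1, adjusted for baseline FMA-UE, reported with a 95% CI. The difference at T2 is secondary.*

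- **Visit.** T1, the end of the intervention, is a natural choice. T2 or the T1/T2 average is acceptable if fixed in advance.
- **Model.** Use ANCOVA at the chosen visit, or a mixed model with T1 and T2 as outcomes, baseline FMA-UE as covariate, Group, Visit and Group × Visit, and unstructured covariance. The single estimate and its standard error pool directly over the planned imputations.
- **Power.** In Sample size, restate power for this 1-df contrast at the N finally confirmed, with the assumed baseline correlation written out and a range shown.
- **Interaction.** It may stay as a secondary description of the profiles.

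**Cost.** Wording and one recalculation. All the measurements are already scheduled in Table 2, so no visit or assessment is added. The real trade-off is that a contrast at one visit loses power if the effect is small there and larger at the other visit, so the choice should follow where benefit is expected and be fixed before unblinding.
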